
### Primary cost-effectiveness outcome measure

The primary cost-effectiveness outcome is cost-utility measured as incremental cost per QALY at 24 months. Utility measured by QALYs will be obtained from EQ-5D 5 L administered at the time intervals described above. Total QALY gain for each group will be calculated by the AUC method. QALYs from short-term impacts immediately following interventions will be estimated from a sub-study using the TTO technique administered in a structured interview. This will provide a more accurate estimate of QALYs than that based solely on the administration of the EQ-5D over the follow-up period. Associated costs will be those resources required to deliver trial interventions, and costs incurred during follow-up for condition-related primary and secondary care use. Intervention-related costs will be based on participant-level data (e.g. operating time, grade of surgeon and protocol deviations), other related hospitalisations and secondary interventions provided in hospital, outpatient visits (number and speciality) obtained from clinical records and the CRF. Unit costs for intervention-related resource use will be calculated according to NHS reference cost schedules [22] or based on study-specific estimates from participating centres. Costs incurred during follow-up will be estimated based on information collected in the PCQ. Use of primary care service (number and type of GP visits), secondary care service (hospital outpatient visits and inpatient stay following surgery) and other healthcare service (e.g. patients’ out-of-pocket health expenses, use of private healthcare) will be collected from part A of the PCQ completed at 6 and 12 months after initial surgery, and at 18 and 24 months after randomisation. Patient time and travel costs and other related societal costs (e.g. time off work) will be obtained from part B of the PCQ completed at 6 months after initial surgery. Unit costs of healthcare services and medications will be based on published sources, such as the NHS reference Healthcare Resource Group (HRG) tariffs, the British National Formulary [23] and Personal Social Services Research Unit [24].

### Secondary cost-effectiveness outcome measures

Difference in mean costs calculated from the NHS perspective and from the societal perspective [both NHS and individual patients)].Longer-term cost-utility reported as incremental cost per QALY at 10 years. Costs and QALY up to 24 months will be based on trial data and those beyond 24 months will be modelled from the literature for each trial intervention

### Safety

For purposes of this protocol:* All adverse events will be recorded as they occur at and around the time of primary or re-intervention surgery, and by recall at 3 months, 12 months post surgery and 24 months post randomisation.* Any serious adverse events will be recorded throughout the duration of the trial.* Serious adverse events exclude any pre-planned hospitalisations (e.g. elective surgery) not associated with clinical deterioration.* Serious adverse events exclude routine treatment or monitoring of the studied indication, not associated with any deterioration in condition.* Serious adverse events exclude elective or scheduled treatment for pre-existing conditions that did not worsen during the study.* Serious adverse events exclude stricture (symptom or urine flow) recurrence which is already documented and monitored within study.

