The target population for this clinical trial is the 30–60 % of men with a bulbar urethral stricture who suffer recurrence after initial surgical treatment, since the best way to treat the recurrent stricture is uncertain. Repeat urethrotomy and open reconstructive urethroplasty are both reasonable options and the choice between the two is the focus of this study. Registry data suggests repeat urethrotomy is most often performed. It is minimally invasive, does not require specialist surgical expertise, and has a short period of catheterisation and recovery [2]. However, the rate of recurrence following the second (first repeat) urethrotomy is reported to range from 50 to 100 % (median 80 %) at 2 years [3]. Subsequent recurrences can lead to a chronic stricture state requiring repeated urethrotomies, on average every 2 years during a man’s lifetime [4]. Each urethrotomy carries a risk of adverse effects including protracted bleeding (6 %) and urinary tract infection (UTI; 10 %), potentially leading to loss of quality of life, unplanned hospital admissions and additional costs [5]. The alternative to endoscopic urethrotomy is reconstructive open urethroplasty. The urethra is approached through a skin incision in the perineum behind the scrotum. The narrowed segment is then identified and reconstructed typically using a patch of graft material to rebuild the diseased area and permanently widen the lumen [6]. The main perceived advantage of open urethroplasty is a potentially higher rate of long-term cure. A median success rate of 90 % freedom from stricture recurrence at 2 years has been reported in two systematic reviews of case series [6, 7] and is consistent between the UK and the United States (US) [8, 9]. Wound infection (5 %) and post-micturition dribble (10 %) are the most frequently occurring adverse effects together with pain at the graft donor site in the mouth [6, 10]. Registry data suggests that endoscopic urethrotomy remains the most frequently used treatment for men with recurrent urethral strictures. Annual hospital episode statistics from NHS England show that 818 urethroplasties of all types were carried out in 2013–2014 compared with 9,663 endoscopic urethrotomies/urethral dilations [2]. In the US, clinician surveys indicate that about 70 % of urologists would advise patients to proceed to repeat urethrotomy on initial stricture recurrence rather than consider urethroplasty [11]. Similarly, men undergoing urethroplasty in the UK have had a median of four previous urethrotomies [12]. In the UK and the US expert opinion has highlighted the perceived underutilisation of urethroplasty surgery [13]. The evidence base needed to decide whether urethroplasty is better than endoscopic urethrotomy for men with recurrent bulbar stricture is limited by lack of head-to-head comparison of the procedures in randomised controlled trials (RCTs) as documented by a Cochrane review [14].

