### Trial interventions

Two surgical interventions will be investigated:Urethrotomy (standard)The standard intervention of endoscopic urethrotomy typically takes 45 minutes under general anaesthesia, with prophylactic antibiotic cover. With the patient’s legs partially elevated in supporting stirrups, the endoscope is passed along the lubricated penile urethra to locate the distal end of the stricture. A fine-calibre wire guide is then passed through the stricture to the bladder. Using this guide, the stricture is progressively divided longitudinally using the mounted scalpel in the dorsal ‘12 o’clock’ orientation until the proximal end of the stricture is reached. For short flimsy strictures, dilatation with the instrument may suffice without making a cut. The instrument is withdrawn and a 16 French calibre silicon catheter inserted through the urethra to the bladder and left on free drainage [15]. The patient recovers on the ward and is discharged according to local practice (NHS median stay is 1 day) usually with the catheter still in place. He returns to hospital after an interval or remains as an inpatient according to local practice (typically 2–3 days) for catheter removal and voiding check and then is followed up by outpatient review and urinary flow rate at 3, 12 and 24 months. According to the clinician’s policy at individual recruiting sites, and patient choice, participants may continue a programme of intermittent self-dilation (ISD) using a plastic catheter following urethrotomy.2.Urethroplasty (experimental)Open urethroplasty involves the reconstruction of the urethra through an appropriately sited longitudinal skin incision made in the perineum beneath the scrotum between the legs. It requires pre-operative X-ray urethrography. The surgery takes 2–3 hours under general anaesthesia with the patient’s legs partially elevated in supports and prophylactic antibiotic given. The bulbar urethra is located through the skin incision and mobilised. The strictured segment is incised longitudinally with the cut extending into visibly healthy urethra proximally and distally. For the majority of cases where the stricture is relatively long and dense, a graft of oral mucosa is inserted to widen the strictured area of urethra (patch urethroplasty) [16]. The graft (typically 5 cm by 2 cm) is harvested according to a standard technique from the inner cheek with the donor site left open to heal spontaneously or closed with sutures according to surgeon practice [17]. The graft is prepared, positioned appropriately, sutured to the cut urethral edges, and stabilised on the deeper tissues within the perineal wound. This incorporates the graft mucosal surface into the lumen of the urethra. For short supple strictures, simple excision of the scarred area and re-joining of the cut ends may be performed without a graft (anastomotic urethroplasty) [18]. A 16 French calibre silicon catheter is then passed to the bladder and left in situ on free drainage. The patient recovers on the ward before discharge home (NHS median stay is 2 days). The patient returns after an interval according to local practice (typically 2–3 weeks) for an X-ray urethrogram to check leak-free healing, and catheter removal. Follow-up comprises outpatient review and urinary flow rate at 3, 12 and 24 months. Some surgeons prefer a further urethrogram or endoscopic examination to be performed at about 12 months to ensure that no recurrence has occurred.Surgeons performing the procedures will be UK consultant, accredited urologists or senior urology trainees under consultant supervision. Endoscopic urethrotomy is a procedure that all operating urologists have competency for and will take place at the hospital site where the participant was randomised. Open urethroplasty is a specialised procedure carried out for trial participants by urologists recognised as being urethral surgeons by their employing NHS organisation. The surgery will be carried out at regional referral centres (which are all registered sites for the OPEN trial) to which participants will be referred using established routine NHS pathways for undertaking this surgery.

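### Non-serious early complications may be detected unequally: the peri-operative recording period is not fixed in days, and routine contacts before 3 months differ by arm

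*Protocol article*

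**What the plan says.** The Safety section sets one rule for both arms: "All adverse events will be recorded as they occur at and around the time of primary or re-intervention surgery, and by recall at 3 months". Recall is repeated at 12 months after surgery and 24 months after randomisation, and serious events are recorded throughout. The peri-operative period is not defined in days.

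The Trial interventions section gives each arm its own early contacts:
- **Urethrotomy.** Discharge follows local practice ("NHS median stay is 1 day) usually with the catheter still in place"). The man then returns, or stays in, "according to local practice (typically 2–3 days) for catheter removal and voiding check".
- **Urethroplasty.** The man recovers on the ward "before discharge home (NHS median stay is 2 days") and comes back once ("typically 2–3 weeks) for an X-ray urethrogram to check leak-free healing, and catheter removal").

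Under Trial procedures, the first scheduled clinic review of adverse events is at 3 months after the intervention in both arms. The Adverse events section requires every event during participation to go on the case report form. Methods/Design states that patients and surgeons are not blinded. The safety profile of each procedure is a secondary objective.

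**The concern.** A non-serious event has to come to the site's notice before it can be recorded. Between about day 3 and month 3, the urethroplasty arm has a routine hospital visit with imaging, and the urethrotomy arm has no routine contact described. A urinary infection treated by a general practitioner on day 10 can be mentioned at that visit in one arm. In the other it rests on what the man remembers at 3 months. Because the peri-operative period has no stated end, each site may decide for itself whether an event reported at catheter removal counts as contemporaneous. Staff know the allocation when they decide.

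At stake is the comparison of early complications. The Background presents the choice as invasiveness against presumed effectiveness, so complication rates are part of the trial's answer. The events most exposed are those both operations can cause. Infection and bleeding are the two the Background names for urethrotomy, at 10% and 6%.

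**Working it through.** The protocol article states no detection rate or power for safety, so there is no figure to reproduce. The check sets the schedules side by side and then illustrates the possible size.

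**Contacts after the primary operation (Trial interventions; Trial procedures)**

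| | Urethrotomy | Urethroplasty |
|---|---|---|
| Median stay | 1 day | 2 days |
| Catheter removal | typically day 2–3 | typically day 14–21, with urethrogram |
| First scheduled adverse event review | 3 months | 3 months |

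For an event on day 10, the next routine contact after urethroplasty is 14 − 10 = 4 to 21 − 10 = 11 days later. After urethrotomy it is about 90 − 10 = 80 days later.

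**Does another instrument close the gap?** A symptom questionnaire is completed 1 week after catheter removal. Its listed content under Trial procedures has no complications item. It falls on day 2 + 7 = 9 to 3 + 7 = 10 after urethrotomy, and on day 14 + 7 = 21 to 21 + 7 = 28 after urethroplasty. The Discussion reports the lowest return for it, 68%. The first cost questionnaire is at 6 months.

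**Illustration 1.** Let p be the same true rate in both arms, b the share of events arising between about day 3 and day 21, d the chance that such an event is picked up at the 2–3 week urethroplasty visit, and s the chance that it is recalled at 3 months. Events outside that interval are taken as fully detected.
- Detected after urethroplasty = p × [(1 − b) + b × d]
- Detected after urethrotomy = p × [(1 − b) + b × s]
- Spurious excess = p × b × (d − s)

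With p = 10%, d = 1 and b = 0.5, the results for urethroplasty against urethrotomy are:
- s = 0.9: 10.0% against 9.5%
- s = 0.7: 10.0% against 8.5%
- s = 0.5: 10.0% against 7.5%

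Over b = 0.25–0.75 and s = 0.5–1.0, the excess runs from 0 to 10 × 0.75 × 0.5 = 3.75 points, a ratio of 1.00 to 1.60. It is zero if recall is complete, or if events are not collected at the catheter visit (then d = s).

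**Illustration 2.** Spread a 10% risk evenly over 30 days, with 90% capture up to the catheter visit and recall after it. Using mid-range days, 2.5/30 = 0.083 and 17.5/30 = 0.583.
- Recall 60%: urethrotomy 10 × (0.083 × 0.9 + 0.917 × 0.6) = 6.25%; urethroplasty 10 × (0.583 × 0.9 + 0.417 × 0.6) = 7.75%; ratio 1.24.
- Recall 30%: 3.5% and 6.5%; ratio 1.86.

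The differences are 1.5 and 3 points. With about 100 men per arm (the target of 200 in Sample size calculation), that is 1.5 to 3 events.

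In both illustrations p = 10% borrows the Background's infection figure for urethrotomy. The values of b, d, s and the capture rates are assumptions with no source in the document.

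**Opposing mechanism.** Contemporaneous recording also applies to re-intervention surgery. Planning rates for re-intervention are 50% and 20%. Counting at most one per man, there are 1 + 0.5 = 1.5 recording periods per man after urethrotomy and 1 + 0.2 = 1.2 after urethroplasty.

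**The case against.** The strongest reply is that the rule is the same in both arms and the difference is one visit. The 3-month review covers the whole early period for everyone, serious events are recorded continuously, and any event a site learns of must be entered. No section says that adverse events are collected at catheter removal. If they are not, this source of inequality disappears. An event at home that is reported at 2–3 weeks is itself recalled, though over days rather than months. The wording of the 3-month form belongs to the full protocol, so the recall may already be prompted.

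Most of this stands as a limit on the claim. It does not remove the point. The duty to report cannot reach an event nobody has mentioned, and continuous recording of serious events does not cover a non-serious infection or bleed. The Discussion shows that catheter-removal dates were entered in the electronic case report form, so the visit is within the trial's data flow. With no length set for the peri-operative period, sites are free to record there or not.

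Four stronger readings are tempting and are not supported:
- **That hospital contact lasts 2–3 weeks after urethroplasty.** Men go home after a median of 2 days and return once.
- **That urethroplasty will look less safe overall.** The extra recording periods at re-intervention push a pooled count the other way. They do not recover a day-10 infection missed after the first operation, so the plausible direction holds only for early complications of the primary operation.
- **That the economic model is biased.** Under Economic analysis, utilities for men with adverse events come from those men's EQ-5D responses. Missing some cases does not by itself shift that mean.
- **That a false ratio of 1.2–1.9 is to be expected.** It reproduces, but rests wholly on assumed capture rates.

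**Conclusion.** The concern holds as a risk of unequal detection, not as a demonstrated bias. The peri-operative recording period is not fixed in days, and the routine contacts before 3 months differ by arm in an open-label trial. Non-serious early complications of the primary operation that either procedure can cause may therefore be recorded unequally, plausibly more often after urethroplasty.

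The size cannot be derived from the document. Under the stated assumptions it is between nothing and a few events per arm. That could distort a comparison of infrequent complications, but it does not touch the primary outcome. The conclusion depends on at least some sites noting events at the catheter-removal visit and on 3-month recall being incomplete. The article settles neither. For all adverse events pooled over follow-up, the net direction is uncertain. The point merits correction because safety is a stated objective and the remedy is cheap.

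**What to change.** On the existing 3-month adverse event review form:
- Ask both arms the same prompted list of named complications for the same fixed periods after the primary operation: up to day 30, and day 31 to 3 months.
- Base the between-arm comparison of early complications common to both operations on that list.
- Describe procedure-specific events (wound, graft donor site) by arm without comparing them.
- Report findings made only at the protocol urethrogram separately.

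Do not place the list on the questionnaire completed 1 week after catheter removal. It falls on different post-operative days in the two arms and would recreate the problem.

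The cost is a few more questions per man on one form and a sentence in the analysis plan, with no added visit. Two limits remain. The information is still recalled, although equally so in both arms. Men already past 3 months would not have the list, and with 214 enrolled by the end of November 2015 they may be many. Because the Discussion says waiting times differ between arms, the number of men with the list should be reported by arm.

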### Recording and reporting serious adverse events or reactions

#### Summary

Research team staff at individual sites will complete the adverse events (AE) section of the relevant CRFs and input the details of the AEs into the database hosted by the Centre for Healthcare and Randomised Trials (CHaRT) in Aberdeen, UK via the secure study website. The CHaRT web-based system will automatically alert the Trial Manager based in the Clinical Trials Unit, Newcastle University, Newcastle upon Tyne, UK if any new AEs are added or any amendments are made to the data in existing ones. The trial management office in Newcastle in conjunction with the Chief Investigator (CI) will have the responsibility for any decision making and forward reporting of AEs. All AEs should be recorded in the CRF. Suspected unexpected serious adverse events (SUSARs) that are considered to be causally related will be separately reported on the specific form. Adverse events that are serious but expected will not be reported on the SUSAR form.

##### Adverse events (AEs)

All AEs during study participation will be reported on the study CRF and entered by local investigators into the trial web management system. The individual investigator at each site will be responsible for managing all AEs according to local arrangements.

##### Serious adverse events (SAEs)

All unexpected SAEs that are related or of uncertain causality during study participation shall be reported to the CI through the study website within 24 hours of the site learning of its occurrence. The initial report will be made by completing the electronic SUSAR form which will automatically send e-mail notification to the Trial Manager and CI in Newcastle. In the case of incomplete information at the time of initial reporting, all appropriate information should be provided as follow-up as soon as this becomes available. Relationship of the SAE to trial participation should be assessed by the investigator at site, as should the expected or unexpected nature of the AE. The Research Ethics Committee (REC) will be notified by the CI (on behalf of the Sponsor; The Newcastle upon Tyne Hospitals NHS Foundation Trust) of all SUSARs within 15 days of the CI becoming aware of the SUSAR (unless urgent safety measures are required, in which case initial notification by telephone will be made immediately the CI becomes aware of the AE, with notice in writing following within 3 days). SUSARs will be reported using the National Research Ethics Committee (NRES) Report of Serious Events Form, version 3, April 2007 [25]. The CI will ensure that the Sponsor is notified of any SUSARs in accordance with local trust policy. Local investigators should report any SUSARs as required by their local NHS Trust Research and Development Office.

### Statistical analysis

The primary outcome, AUC for the ICIQ-Male SF symptom score, will be generated for each participant using the trapezoidal rule. Symptom score data for participants who have missed a scheduled time point will be estimated using a multiple imputation approach to make use of partial outcome data [26]. Sensitivity analyses will be conducted to assess the robustness of the treatment effect estimate to these approaches. The primary outcome measure will be analysed using linear regression with adjustment for the minimisation variables [site of recruitment and time since last procedure (<12 months or ≥12 months)]. The main statistical analyses will be based on all participants as randomised, irrespective of subsequent compliance with the treatment allocation. Secondary outcomes will be analysed using generalised linear models with adjustment for minimisation and baseline variables as appropriate. All estimates will be presented with 95 % confidence intervals. Subgroup analyses will explore the possible modification of treatment effect by clinically important factors; time since last procedure (<12 months or ≥12 months) as a global measure of stricture severity, age, stricture location, and length. This will be done by including treatment-by-factor interactions in the model. All analyses will initially be performed on an intention-to-treat basis. We will consider additional analyses such as per-protocol depending on the levels of compliance with allocated treatment. Further analysis will explore the impact of variations in treatment delivered; such as use of anastomotic urethroplasty, use of intermittent self-dilatation after urethrotomy, and delay between decision to treat and undergoing the intervention. From the initial phase of recruitment we will report estimates of recruitment rates and potential participant availability, together with appropriate confidence intervals. There are no planned interim outcome analyses; all analyses will occur following completion of trial follow-up. Interim analyses will be performed if requested by the Data Monitoring and Ethics Committee (DMC). All analyses will be outlined in detail in a pre-specified statistical analysis plan.

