### Randomisation process

Eligible and consenting participants will be randomised to one of the two intervention groups using the 24-hour telephone Interactive Voice Response randomisation application or via the web-based application, both hosted by the Centre for Healthcare Randomised Trials (CHaRT) at The University of Aberdeen, UK. The randomisation algorithm will use recruitment site and time since last procedure (<12 months or ≥12 months) as minimisation factors to allocate treatment to intervention and standard groups in a 1:1 ratio. A random element (20 %) will be incorporated into the randomisation algorithm, so that one in five allocations will be randomly switched. The Principal Investigator (PI) at site, or individual with delegated authority, will access the telephone or web-based system when an eligible participant has consented to participate in the study. Patient screening identification, initials, recruiting site and time since last intervention (stratifying variables) will be entered into the voice-activated or web-based system, which will return the allocation status. Participants will be informed of their allocated treatment group following randomisation and arrangements will be made to carry out the procedure according to the standard process of care at the recruiting site.

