### Primary effectiveness outcome measure

Difference in trajectory of symptom control measured by area under the curve (AUC) of the ICIQ-Male SF symptom score [19] completed by participants during routine clinic visits or by postal or online questionnaires at baseline, immediately prior to surgery, 1 week after catheter removal, at 3, 6, 9, 12 months after intervention, and at 18 and 24 months after randomisation, and additionally prior and subsequent to any surgical re-intervention. The ICIQ-Male SF modular questionnaire has been validated in this patient group [20]. The trial duration allows for follow-up of all men at 24 months after randomisation. We will also collect longer-term follow-up data for those men who undergo their allocated intervention earlier during the recruitment window by completion of additional outcome questionnaires at 24 months post surgery and at the end of the study (December 2017).

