### Sample size calculation

We initially planned to recruit 500 participants to the study. This used the assumption that the standard deviation (SD) of the primary outcome measure (ICIQ-Male SF questionnaire score 0–24) would be 0.3. Using this figure with 90 % power (two-sided 5 % significance level), 235 participants per group (470 in total) would have been required. This would equate to being able to detect at least a 0.1 difference in the AUC on the standardized 0–1 utility scale, assuming a SD of 0.33 or less. The SD of the ICIQ-Male SF symptom AUC in a previous study was 0.15 [20]. Given our lack of more precise information, we initially conservatively allowed for a larger SD in recognition of the less selected, more pragmatic (i.e. more representative) population to be recruited to this trial and the shorter follow-up period in the previous study. Such a difference in symptom burden and associated QoL has been observed in different clinical areas for health-related quality-of-life (HRQoL) measures [27]. In terms of treatment effect size, this is in the small to medium range as observed in other clinical studies [28]. To allow for the anticipated approximately 5 % of participants for whom outcome data is completely missing, and therefore the AUC cannot be calculated, it was initially proposed to randomise 500 participants. The slower than initially expected recruitment rate has allowed us to use blinded trial outcome data to provide a more precise estimate of the SD. We have calculated the SD of the patient-reported symptom score (primary outcome measure) from 69 active OPEN participants who have submitted at least one post-operative measure (220 measurements in total). The re-calculation gives an SD value of 0.165, which reduces to 0.15 when adjusted for baseline score and centre, considerably smaller than the assumed value of 0.33, which was used in our initial calculations. Using this SD in our sample size calculation would indicate a target population of 96 participants. However, no 18 or 24 month data are currently available and variability would be expected to increase over time. Allowing for this and other factors increasing variability we have assumed a SD of 0.21 or less. This would require 186 randomised men with complete follow-up inflated to 200 in total to allow for loss to follow-up. Based on findings from recruitment to the ProtecT trial, which randomises between surgery and less invasive options for men with localised prostate cancer, we originally conservatively estimated a 55 % agreement to participate rate amongst those eligible requiring 910 men to be approached [29]. We have reassessed this in the light of slower than anticipated recruitment rate from screening data from the trial now available to us showing a 22 % agreement to participate rate. For the qualitative interview study we estimate, based on previous experience in such methodology, that up to 10 men who agree, and up to 10 men who do not agree to be randomised and up to 12 purposively sampled specialist and general urologists will be required to achieve data saturation for thematic analysis. The trial is also secondarily powered to determine whether the use of urethroplasty will result in a 30 % (from 50 % to 20 %) reduction in need for further intervention at 2 years compared to urethrotomy as a secondary outcome. To detect this difference using the binomial test of proportions with 90 % power at the 5 % significance level would require 48 men to complete the study in each arm.

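### The stated primary AUC model leaves out the baseline ICIQ-Male SF score; adding it is a nearly free gain in precision, bounded at about 17% of variance

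*Protocol article*

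**What the plan says.** The Statistical analysis section states the primary model with its covariates: "The primary outcome measure will be analysed using linear regression with adjustment for the minimisation variables". Brackets after these words name them as recruitment site and time since last procedure, the latter split at 12 months. For the other endpoints the same section says: "Secondary outcomes will be analysed using generalised linear models with adjustment for minimisation and baseline variables as appropriate". Baseline variables are thus mentioned for secondary outcomes and not for the primary one.

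Under Randomisation process, the algorithm "will use recruitment site and time since last procedure (<12 months or ≥12 months) as minimisation factors". The baseline score is not among the factors.

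Under Primary effectiveness outcome measure, the ICIQ-Male SF is "completed by participants during routine clinic visits or by postal or online questionnaires at baseline, immediately prior to surgery", and then at further points to 24 months after randomisation. The Discussion explains that the primary analysis is anchored at randomisation, and that waiting times for surgery differ between centres and between arms.

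Under Sample size calculation, blinded data from 69 men (220 measurements) are summarised: "The re-calculation gives an SD value of 0.165, which reduces to 0.15 when adjusted for baseline score and centre". A target of 96 follows. It is then set aside for a planning SD of 0.21 or less, which gives 186 men with complete follow-up and 200 randomised. The article does not say whether 0.21 is before or after adjustment for baseline.

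**The concern.** A man's baseline score is one of the values from which his AUC is built, and it is likely to be correlated with his later scores. It is therefore a natural covariate for the primary regression. Neither minimisation factor is a direct measure of it, so its balance between arms is left largely to chance in a trial whose target fell from 500 to 200 men.

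The article's own re-estimation used the baseline score as an adjuster, and the secondary models may use baseline variables. As written, the primary outcome is the one analysis for which baseline adjustment is not mentioned. At stake are the width of the primary confidence interval and the protection of the estimate against a chance difference in starting symptoms.

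**Working it through.** **Inputs** (Sample size calculation, Randomisation process): difference 0.1 on the 0–1 scale, two-sided 5%, power 90%, 1:1 allocation; blinded SD 0.165 unadjusted and 0.15 adjusted for baseline and centre; planning SD 0.21.

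**Step 1: reproduce the plan's figures.** n per arm = 2(1.96 + 1.2816)² × (SD/0.1)² = 21.02 × (SD/0.1)².

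- SD 0.21: 21.02 × 4.41 = 92.7, so 93 per arm and 186 in total. This matches the article.
- SD 0.15: 21.02 × 2.25 = 47.3, so 48 per arm and 96 in total. This matches the article.
- SD 0.165: 21.02 × 2.7225 = 57.2, so 58 per arm and 116 in total.

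The intermediate figure of 96 therefore rests on the SD adjusted for baseline and centre. The adopted figure of 186 rests on 0.21.

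**Step 2: the joint effect of baseline and centre.** (0.15/0.165)² = 0.826, a fall in variance of 17.4%.

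**Step 3: what baseline alone can add.** Take centre in the re-estimation to be the same as recruitment site in the model. Site is then already adjusted for, and only the baseline share of the 17.4% is still to be gained. The article does not split it, so let baseline account for a share s from 0 to 1 (an assumption covering the whole range).

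**Step 4: carry this to the adopted sample size.** Suppose 0.21 is before baseline adjustment, and suppose the proportional reduction seen in the post-operative scores also applies to the 24-month AUC. Then SD after adjustment = 0.21 × √(1 − 0.174s). Power with 93 per arm = Φ(0.1 / (SD × √(2/93)) − 1.96).

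| Baseline share s | SD | Total N for 90% power | Power with 186 men |
|---|---|---|---|
| 0 | 0.210 | 186 | 90.1% |
| 0.5 | 0.201 | 170 | 92.5% |
| 1 | 0.191 | 154 | 94.7% |

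**Step 5: the direct weight of the baseline point.** Under the trapezoidal rule this is half the interval from baseline to the next measurement, divided by 24 months. Waiting times are not given. Assuming 1 to 6 months, the weight is 0.5/24 = 2% to 3/24 = 12.5%. The larger route by which a baseline difference could reach the AUC is through correlated later scores, which the article does not quantify.

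**The case against.** The strongest case against the point is that adjusting for the minimisation factors is a valid specification. The bracket defines those factors and does not say that nothing else may enter. The article also refers detail to a separate statistical analysis plan that is not shown. That plan may add the baseline score. Even so, the article states the primary covariates and mentions baseline variables only for secondary outcomes, so this is a stated choice that can be improved and not plain silence.

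Several stronger readings are tempting, and the documents do not support them.

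- **That the omission costs 21% in variance ((0.165/0.15)² = 1.21), or 116 men against 96.** That compares adjustment for baseline and centre with adjustment for neither. The stated model already includes site, so these figures are only an upper bound. They also come from individual post-operative scores with no 18- or 24-month data, not from the 24-month AUC.
- **That the trial misses its stated power.** The 96 was not adopted. The planning SD of 0.21 lies above even the unadjusted 0.165, at which 93 per arm would have about 98.5% power. Power falls below 90% only if 0.21 presumes baseline adjustment. In the extreme case, where baseline also explains the whole 17.4%, SD is 0.231, power with 186 men is 83.9%, and 226 would be needed. Neither condition is stated.
- **That the treatment estimate is biased.** Randomisation keeps it unbiased on average, and the confidence interval allows for chance imbalance. The issue is efficiency.
- **That the QALY analysis and the imputation model have the same fault.** The article gives no covariates for either, and a condensed article may leave these to the fuller plan.

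**Conclusion.** The point holds as a free improvement. The primary model, as stated, does not include the baseline ICIQ-Male SF score, although the score is collected, forms part of the outcome, and was used in the sample size re-estimation. Adding it would reduce variance by between 0 and about 17%. If 0.21 is before baseline adjustment, that takes power with 186 men from 90.1% to at most about 94.7%.

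The bound rests on three assumptions: centre and recruitment site are the same variable, the reduction seen in post-operative scores carries over to the AUC, and the planning SD scales in the same proportion. The primary analysis is valid without the change, and the documents do not show a sample size error.

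**What to change.** Before unblinding, state the primary model as AUC regressed on allocation, baseline ICIQ-Male SF score, time since last procedure and site. In the sample size section, add whether the planning SD of 0.21 is before or after adjustment for baseline.

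The cost is two sentences and one degree of freedom in the model. The score is already scheduled for collection at baseline, and the article plans all analyses for after follow-up is complete. Fixing the covariate in advance also removes any suspicion that it was chosen after seeing the results, which matters in a trial where patients and surgeons cannot be blinded.
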